### Data management and statistical analysis

We will use an electronic case report form to collect data, and an electronic database will be subsequently generated. All the investigators need to be authorised to access the data and will be required to maintain data confidentiality. A periodic indication to update outcomes’ information during the follow-up will also be set up. After completion of the study, data will be stored for at least 20 years at a central data drive at the Peking Union Medical College Hospital. The datasets used and/or analysed during the current study can be obtained from the principal investigator on reasonable request. Moreover, a written, signed data-sharing agreement will be required to get data access.

The variables will be described according to the distributions, namely, mean±SD (range) for normally distributed continuous variables, otherwise they are described as medians and IQRs. Counts (percentages) will be used to present discrete variables. Methods for comparisons of variables between two groups will also be determined according to the data types. For oncology outcomes, including recurrence-free survival, overall survival and disease-specific survival, we will use the Kaplan-Meier method (log-rank test). The univariate analysis will be performed to screen factors that should be subjected to multivariate analysis, and we set the cut-off p values as 0.10 in univariate analysis. The Cox regression model or logistic regression model will be conducted in multivariate analysis. SPSS (V.20.0; SPSS), GraphPad Prism (V.8.0; GraphPad Software, La Jolla, California, USA) or STATA (SE V.12, StataCorp) software will be applied to perform the statistical analysis when appropriate. We set the statistical significance cut-off as 0.05 (two-tailed p value).

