#### Management in case of patients who could not complete pulmonary function test

In patients who may not be able to receive pulmonary function tests due to bleomycin-induced acute lung injury, arterial blood gases and high-resolution pulmonary CT will be performed to indirectly examine the pulmonary function. Meanwhile, it is also an adverse event that will be recorded in this trial. Pulmonary function tests will be performed after recovery or until those patients can complete this examination. For patients whose general condition has deteriorated due to MOGCT progression, if such patients had been enrolled in this trial, they would have recorded baseline and dynamic pulmonary function tests until they could not finish the pulmonary test. If they have not already finished the complete treatment for MOGCT and cannot continuously receive bleomycin-based chemotherapy, these adverse events will be recorded as positive events during the trial to evaluate the safety of nintedanib.

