#### Follow-up data collection

The disease-specific data, including tumour stage, pathological subtypes of MOGCTs, tumour markers’ value, surgical options and chemotherapy response, etc, will further be recorded in detail. The patients need to routinely follow-up in outpatient before each chemotherapy cycle. The frequency of outpatient follow-up after finishing chemotherapy is set as follows: every 3 months within 3 years after treatment and every 6 months between 3 and 5 years after treatment. Additional follow-up will be provided in case of special conditions, such as severe chemotherapy side effects or tumour recurrence. A telephone follow-up will be a supplementary option for those patients who follow-up in local hospitals or miss the appointment day. Importantly, the patients’ smoking status, whether they receive oxygen therapy, and/or chest radiation before or during the treatment will be recorded in detail due to these factors may have a synergised effect with bleomycin.

During each follow-up, the patients will need to report the oncology outcomes, pulmonary function, QoL, menstrual conditions and fertility outcomes for childbearing patients with the desire for fertility. The interval between bleomycin-containing chemotherapy and the onset of lung injury will be exactly recorded during the trial. The QoL assessment will be based on the general conditions and self-report questionnaires listed as follows.

The privacy of patients will be rigorously protected throughout the whole study process. Any statistical analysis or publications of data can only be presented in an anonymisation format.

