### Outcomes

#### Primary outcomes

The primary outcome of the study is the declined degree of FVC in MOGCT patients who receive BEP chemotherapy revealed by respiratory function test. The secondary outcomes are the decline of other pulmonary function indices (FEV1; FVC pred% and DLCO), the safety of nintedanib treatment, oncological and fertility outcomes, and QoL in MOGCTs patients.

The safety assessment of nintedanib is measured by patients’ vital signs, auxiliary examinations and AEs. The auxiliary examinations include blood tests (routine analysis, liver and kidney function, etc), urine and stool examinations. We will record any AE during the treatment and follow-up period. The definition and classification of AEs based on the CTCAE5.0. Treatment will be continued in case of grade 1 or tolerable grade 2 AEs, and temporary termination of treatment will be applied in case of the first occurrence of intolerable grade 2 or grade 3 AEs until recovery to grade 0–1 or grade 2 AEs. However, permanent termination of nintedanib medication will be considered on the second time of intolerable grade 2 or grade 3 AEs, no matter the previous toxicities or newly identified toxicities.

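### The article names no regression model suited to its continuous primary outcome, FVC decline, and no baseline-adjusted FVC analysis, although baseline and serial FVC are collected

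*Protocol article*

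**What the plan says.** The Primary outcomes section defines the endpoint: "The primary outcome of the study is the declined degree of FVC in MOGCT patients who receive BEP chemotherapy revealed by respiratory function test". This is a continuous change-type measure.

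The Data management and statistical analysis section says three things that bear on its analysis:

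- On description: "The variables will be described according to the distributions, namely, mean±SD (range) for normally distributed continuous variables, otherwise they are described as medians and IQRs".
- On comparison: "Methods for comparisons of variables between two groups will also be determined according to the data types".
- On modelling: "The Cox regression model or logistic regression model will be conducted in multivariate analysis", after univariate screening for which "we set the cut-off p values as 0.10 in univariate analysis".

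The same section names Kaplan-Meier and the log-rank test for the oncology outcomes. It names no test or model for FVC.

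On the data available, the Participants section sets a minimum FVC of 45% of predicted for entry, so every patient has a baseline value. The Follow-up data collection section has lung function followed over time: "During each follow-up, the patients will need to report the oncology outcomes, pulmonary function, QoL, menstrual conditions and fertility outcomes". Visits are three-monthly for 3 years and six-monthly to year 5. The section on patients who cannot complete the test also refers to baseline and serial measurement: "they would have recorded baseline and dynamic pulmonary function tests until they could not finish the pulmonary test". That sentence is written for patients who deteriorate from tumour progression, so the follow-up section is the better source for the cohort as a whole.

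**The concern.** The article is specific about the models for secondary outcomes and about covariate selection, but what it fixes does not fit its own primary outcome. A Cox model needs a time to event and a logistic model needs a binary response. FVC decline is neither. What remains for FVC is the general two-group comparison.

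Baseline FVC would be expected to be a strong predictor of follow-up FVC. Subtracting baseline uses that information only partly, because it fixes the slope of follow-up on baseline at 1. If the true slope is lower, the change score stays correlated with baseline, and a chance imbalance in baseline FVC carries into the estimated effect. Adjustment removes that and narrows the interval. This matters in a trial of 128 patients whose own limitations statement cites the rarity of the disease as an obstacle to enrolment.

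The p<0.10 screening rule is a second poor fit. If it were carried over to the primary comparison, the adjustment set would depend on the data, and baseline FVC could drop out by chance.

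**Working it through.** **Inputs.** The article gives neither an SD of FVC (or of its change) nor a baseline to follow-up correlation. The sample size section cannot supply them. It works from declines of over 8% and 4%, a margin of 10%, one-sided alpha 0.025 and 53 per group, with no SD.

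- Read as proportions without decline (0.92 and 0.96), and with the printed power of 0.09 taken as 0.90, the variance term is 0.92×0.08 + 0.96×0.04 = 0.112. Then n = 0.112 × (1.960 + 1.282)² / 0.14² = 60.04, so 61 per group and not 53.
- Read as means at 90% power, 53 per group would imply an SD of 22.2, 15.9 or 9.5, according to whether the distance to the margin is taken as 14, 10 or 6 points.

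No usable SD follows from this. The mismatch is a separate matter and does not decide this point.

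**Formulas.** Let s₀ and s₁ be the SDs of baseline and follow-up FVC and r their correlation.

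- Unadjusted change score: variance s₀² + s₁² − 2r·s₀·s₁.
- ANCOVA with baseline as covariate: residual variance s₁²(1 − r²).
- Difference: (s₀ − r·s₁)², which is never negative. Apart from the one degree of freedom spent on the covariate, ANCOVA is never less precise.
- With equal SDs s: 2s²(1 − r) against s²(1 − r²), a ratio of (1 + r)/2.
- Equivalent gain in patients: 2/(1 + r) − 1.

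**Results over an assumed range of r.**

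| r (assumed) | Variance ratio | Equivalent gain | Of 128 patients | 53 per arm becomes |
|---|---|---|---|---|
| 0.7 | 0.85 | 17.6% | 23 | 46 |
| 0.8 | 0.90 | 11.1% | 14 | 48 |
| 0.9 | 0.95 | 5.3% | 7 | 51 |

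**What this means for power (illustration only).** Take a 4-point difference (8% minus 4%), 53 per arm and two-sided 0.05, with power Φ(4 / (SD·√(2/53)) − 1.96). For ANCOVA, the SD is multiplied by √((1 + r)/2).

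| Assumed SD of change | Unadjusted | ANCOVA, r = 0.9 | r = 0.8 | r = 0.7 |
|---|---|---|---|---|
| 6 | 92.9% | 94.1% | 95.1% | 96.1% |
| 8 | 73.0% | 75.2% | 77.4% | 79.7% |
| 10 | 53.9% | 56.1% | 58.3% | 60.8% |

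At SD 8, for example, 8 × √(2/53) = 1.554. Then 4/1.554 = 2.574, and Φ(2.574 − 1.96) = 0.730.

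**The case against.** The strongest reply is that this is a journal article. The form of the primary model and its covariates commonly sit in the full protocol or SAP, neither of which is shown, so silence on them is no fault. That stands against any claim that the sponsor has no primary model. It does not answer the narrower point: the article does fix models and a selection rule, and those do not suit its primary outcome.

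A second reply is that the Cox and logistic sentence follows the survival outcomes and may concern only prognostic factors for oncological and binary endpoints. That is a fair reading. It leaves FVC with the general two-group rule alone.

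A third is that the gain is small and rests on assumptions. This stands. At r = 0.9 and SD 8, power moves only from 73.0% to 75.2%. The ratio assumes equal variances and absolute change. If decline means per cent of each patient's own baseline, it does not carry over directly.

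Some stronger readings are tempting but not supported:

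- A reader might infer that the primary test is unadjusted and will be picked after looking at the distribution. The article never says unadjusted. It ties comparisons to data types, which are known in advance. The distribution rule governs description, and only the word also links the two sentences.
- A reader might infer that baseline FVC is ignored. A decline already uses it by subtraction.
- A reader might infer that FVC will be dichotomised to fit a logistic model. The percentages without an SD in the sample size section make one wonder, but nothing says so.
- A comparison with raw follow-up values would show a variance reduction of r², or 49% to 81% for r of 0.7 to 0.9. Nobody proposes that analysis, so the figure is not the relevant one.

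**Conclusion.** The point holds as an avoidable loss of precision; it does not make the comparison invalid. The article leaves its continuous primary outcome to a generic two-group comparison, names only regression models that do not fit it, and mentions no baseline-adjusted FVC analysis although the data for one are collected. Under equal variances, absolute change and an assumed correlation of 0.7 to 0.9, adjustment would cut the variance by 5% to 15% relative to an unadjusted change score, the equivalent of 7 to 23 more patients out of 128. The true size cannot be derived from the document. A different primary analysis may already be written in an unseen SAP. If so, the article should be brought into line with it.

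**What to change.** Name one primary analysis: ANCOVA of FVC change on arm and baseline FVC, or a mixed model for repeated measures with the same terms. Report the adjusted mean difference with its 95% CI at a visit stated in advance. Age may be added as a prespecified covariate. State that the p<0.10 screening rule does not apply to this analysis, and that the Cox and logistic models are for time-to-event and binary outcomes. Keep the simple two-group test as a sensitivity analysis.

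Baseline FVC is enough for the remedy. Height and a number of cycles fixed before randomisation are not documented as collected, so the model should not depend on them.

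The cost is one paragraph of analysis text, settled before unblinding, with no new data or visits.

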#### Harms

The safety of nintedanib in treating IPF has been confirmed in previous clinical trials.^16^ The AEs are usually mild and tolerable. The most common AEs of nintedanib therapy are as follows (incidence ≥5%): diarrhoea, anorexia, sickness, vomiting, abdominal pain, headache, elevated liver enzyme, weight loss or hypertension. Other rare AEs reported in previous research include haemorrhage, gastrointestinal perforation, elevated bilirubin levels and cardiac toxicity. However, currently, there has been limited data on the safety of nintedanib in MOGCT patients receiving bleomycin-based chemotherapy. Therefore, unpredicted AEs may be found during this trial, and all the AEs observed during the study period will be treated according to the clinical practice. Especially, for MOGCT patients receiving bleomycin-based chemotherapy, the benefit of prevention of bleomycin-induced pulmonary toxicities would be greater than the risk and the harms of nintedanib itself.

### Ethics and dissemination

The Ethics Committee of Peking Union Medical College Hospital has approved the study (I-23PJ400). Written informed consent will be obtained from all participants/guardians. Study results will be submitted to peer-reviewed medical journals for publication and presented at academic conferences. The study will be conducted according to the principles of the Declaration of Helsinki.

### Current status

Participants’ enrollment is planned to start on 1 October 2023 and end on 1 April 2026.

## Discussion

At present, bleomycin-induced pulmonary fibrosis remains a severe chemotherapy AE that significantly impairs the therapeutic efficacy and QoL in MOGCT patients. It was estimated that 8% of patients who received bleomycin may develop varied degrees of pulmonary fibrosis, and nearly 2% were lethal.^29^ Although some optional chemotherapy regimens were proposed to decrease chemo toxicities in MOGCT patients, bleomycin is a crucial and irreplaceable regimen for chemotherapy in MOGCTs patients.^31 32^ Nonetheless, the role of bleomycin is more important for recurrent MOGCTs due to dissatisfactory responses to other regimens.^6 12^ Therefore, how to alleviate pulmonary fibrosis during bleomycin-containing chemotherapy in MOGCTs has always raised great concerns.

The metabolism of bleomycin in the lung is poor because of the low activity of detoxifying enzymes and bleomycin hydrolase.^8^ Hence, the accumulation of bleomycin in the lung, impairs the vascular system, resulting in the aggregation of inflammatory cells and fibroblasts into the lung tissue, which eventually leads to pulmonary fibrosis.^33^ Nonetheless, the exact mechanisms of pulmonary fibrosis development remain unclear, and the time between bleomycin medication and pulmonary fibrosis varies greatly among different patients.^34^ Routine prophylactic administration of antifibrosis drugs in patients receiving bleomycin may be practical due to the availability for early identification of high-risk patients. In several clinical trials of nintedanib in treating progressive fibrosing interstitial lung diseases or IPF, nintedanib showed a significantly lower reduction in pulmonary function.^18 35^ Furthermore, nintedanib has been showing promising therapeutic efficacy in treating fibrosis caused by bleomycin-containing chemotherapy and potential additional benefits in combination with common chemotherapy regimens in cancer patients.^18–20^ Besides, these studies showed relatively minor AEs of nintedanib, revealing the safety of medication in targeted treating patients.^35^

However, currently, there is limited evidence of nintedanib for the prevention or treatment of bleomycin-induced pulmonary fibrosis in MOGCT patients. There has been only limited low-grade evidence originating from case reports. Our prospective, double-blinded, randomised controlled trial aims to provide high-quality treatment on this issue, which will be helpful in the management of the severe AEs caused by bleomycin-containing chemotherapy in this population. Nevertheless, one major limitation of this study is the single-centre setting, further multicentre prospective trials should be conducted.
